### Recruitment {15}

Participants will be recruited over 24 months from clinics, inpatient units, and community residential homes for people with IDD.

## Assignment of interventions: allocation

### Sequence generation {16a}

Participants will be randomly assigned to receive either active or sham tDCS using block randomisation to ensure that an equal number of participants is assigned to each study arm. The research assistant or trial coordinator will be initially blind to the allocation sequence.

### Concealment mechanism {16b}

The allocation sequence will be communicated to the research assistant or trial coordinator after the completion of baseline measures including BPI-S, BIS-11 and MOAS.

### Implementation {16c}

A member of the research team other than the principal investigator will generate the allocation sequence. The study’s research assistant or coordinator will enrol participants, complete the outcome measures, and administer the interventions.

## Assignment of interventions: blinding

### Who will be blinded {17a}

This a single-blinded study where participants will be blinded to treatment allocation. Professionals who complete MOAS and BPI-S will also be blinded to treatment allocation. To minimise bias, the principal investigator and research assistant will be initially blinded to the allocation sequence. This will be generated by a Queen’s University independent faculty member who is not involved in the study, and then communicated to the research assistant administering the intervention after the completion of baseline measures. It is anticipated that having the research assistant unblinded is unlikely to introduce assessment bias since all the study questionnaires will be completed by the participants and professionals involved in their care, who will be blinded to the treatment allocation. Participants will only be unblinded to the treatment allocation if they developed a serious adverse reaction such as self-harm or serious violence. To assess the robustness of blinding, participants will be asked to guess their treatment allocation after the last tDCS session.

### Procedure for unblinding if needed {17b}

As the study is single-blinded, the treatment administrator will always know what treatment arm the participants are in, so that in the event of an emergency, administrators can immediately unblind the participant and/or emergency personnel.

## Data collection and management

### Plans for assessment and collection of outcomes {18a}

This information is provided under “Participant timeline” section of the protocol.

### Plans to promote participant retention and complete follow-up {18b}

The research team will work closely with participants and their caregivers and substitute decision-makers, where applicable, to promote retention and complete follow-up. A travel allowance is available to those who are unable to travel to the study administration site.

### Data management {19}

Access to electronic and paper data will be limited to the research team. The data will also be accessible to the research governance team at Providence Care Hospital and Queen’s University to ensure the quality of research conduct. The electronic data will be encrypted and stored in a password-protected computer. A backup copy will be stored in a password-protected storage device. Paper files will be stored in a locked filing cabinet at Providence Care Hospital. A master file linking identify codes with participant identifiers, accessible only by the principal investigator and research coordinator, will be stored separately from the study data.

### Confidentiality {27}

Access to the participants’ medical records and study data will be limited to authorised research personnel. Access to electronic data will be password protected and auditable. Electronic data will be stored on a hospital or other institutional network with firewalls and other security and back-up measures in place. Data stored on laptops or mobile devices will be encrypted. Paper copies of study data will be stored in locked filing cabinets in a secure location at Providence Care Hospital in Kingston Ontario. A master linking logs with identifiers, accessible only by the principal investigator and research coordinator, will be stored separately from the study data.

### Plans for collection, laboratory evaluation, and storage of biological specimens for genetic or molecular analysis in this trial/future use {33}

Not applicable.

## Statistical methods

### Statistical methods for primary and secondary outcomes {20a}

Behavioural outcome measures will be analysed using the Statistical Package for Social Sciences (SPSS; Version 26). A 2 × 2 Repeated Measures ANOVA will be performed with group allocation (active tDCS vs. sham tDCS) and time (pre- vs. post-tDCS stimulation). Post tDCS measures for MOAS, SST, and BPI-S will be treated separately as repeated measures. Total scores on BIS-11 will be entered into the analysis as a covariate. Significant main effects and interactions will be explored using simple effects analysis. For instance, within-subject factors will be used to compare changes in outcome variables between the groups over time. A greater reduction in the total scores on MOAS in the active tDCS group than the sham tDCS group would be considered a successful primary outcome. Greater reductions in the total scores on BPI and greater increases in Stop Signal Reaction Time in the active tDCS group than the sham tDCS group would be considered successful secondary outcome. A *p* value of < 0.05 will be considered as statistically significant for the primary outcome measure. For secondary outcomes, multiple comparisons will be controlled for with Bonferroni correction and a *p* value of less than 0.0125 will be considered statistically significant.

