### Eligibility criteria {10}

The inclusion criteria are as follows: (i) adults aged between 18 and 65 with mild IDD, (ii) a history of at least one incident of aggression in the last month, and (iii) consent to participate in the trial by the individual or their substitute decision-maker if they lack the capacity to consent to participate in research.

The exclusion criteria are as follows: (i) a history epilepsy, significant head injury or other neurological conditions, or brain surgery; (ii) having a metal in the brain or skull, a cardiac pacemaker, a central line, or a cochlear implant; (iii) current history of drug or alcohol misuse; and (iv) a history of adverse reaction to tDCS or having a sensitive scalp. Table 1 provides more information about the inclusion and exclusion criteria. A tDCS safety questionnaire will be administered to identify those who meet the exclusion criteria.

**Table 1 Tab1:** Inclusion and exclusion criteria

Inclusion criteria	Exclusion criteria
Adults aged 18–65 years	History of epilepsy or seizures
Diagnosis of a mild intellectual developmental disability	History of acquired brain injury
History of 1 or more incidents of aggression in the last month	Having metal in the brain/skull, e.g. splinters, fragments, or clips
Consent to participate in the trial by the individual or their substitute decision-maker	Having a cochlear implant
	Having an implanted neuro-stimulator (e.g. direct brain stimulation, epidural/subdural stimulation, vagal nerve stimulation)
	History of brain surgery or procedure
	History of severe adverse reaction to tDCS
	Having a cardiac pacemaker or intracardiac lines
	Current alcohol or drug misuse
	Having a sensitive scalp

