### Outcomes {12}

#### Primary outcome measure

##### Aggression

The *Modified Overt Aggression Scale* (MOAS) [20] will be used as a repeated measure to assess aggressive behaviours at baseline, 1 week (day 10), and 1 month (day 38) following the last tDCS treatment. MOAS is an informant-rated scale which will be completed by a member of care staff who have professional knowledge of the participant. MOAS has four domains (Verbal Aggression, Aggression Against Property, Autoaggression, and Physical Aggression) which are weighted and each rated on a 5-point scale (0–4). Scoring of MOAS yields weighted scores, total and by domain. MOAS is considered to be a reliable measure of aggressive behaviours in people with IDD [21].

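### The primary MOAS outcome has two post-treatment visits, but the planned ANOVA has room for one, and the plan does not say which visit, or what combination of the two, decides success

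*Protocol article*

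**What the plan says.** **Schedule.** Under Outcomes {12}, MOAS is the only primary outcome. It is an informant-rated scale that "will be used as a repeated measure to assess aggressive behaviours at baseline, 1 week (day 10), and 1 month (day 38") after the last session. That is three assessments, two of them after treatment.

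**Model.** Statistical methods {20a}: "A 2 × 2 Repeated Measures ANOVA will be performed with group allocation (active tDCS vs. sham tDCS) and time (pre- vs. post-tDCS stimulation").

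**Handling of the post-treatment values.** Same section: "Post tDCS measures for MOAS, SST, and BPI-S will be treated separately as repeated measures".

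**Success rule.** Same section, with the closing noun omitted: "A greater reduction in the total scores on MOAS in the active tDCS group than the sham tDCS group would be considered a successful primary". No visit is named.

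**Significance.** For the primary outcome, a p "value of < 0.05 will be considered as statistically significant for the primary outcome measure". Adjustment is limited to the other outcomes: "For secondary outcomes, multiple comparisons will be controlled for with Bonferroni correction", at a threshold of 0.0125. The total score on BIS-11 enters as a covariate.

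**The concern.** The model and the schedule do not fit each other. A pre/post factor needs exactly one post-treatment value per participant, and MOAS supplies two. The article gives no rule for getting from two values to one: it names no visit, no average and no requirement that both visits succeed. As written, an analyst could run the model with day 10, with day 38, or with both, and any of these would comply with the plan.

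What is at stake is the trial's one confirmatory claim. If the visit can be chosen after results are known, or if a favourable result at either visit counts, 0.05 is no longer the chance of a false positive. Even without deliberate selection, two compliant analysts could report opposite primary conclusions when the visits disagree.

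This is more than detail left to a separate analysis plan. The article commits to a specific model, and that model conflicts with its own assessment schedule.

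**Working it through.** **1. Inputs**

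| Input | Value | Source |
|---|---|---|
| MOAS assessments | baseline, day 10, day 38 | Outcomes {12} |
| Time levels in the model | 2 (pre, post) | Statistical methods {20a} |
| Primary alpha | 0.05, not divided | Statistical methods {20a} |
| Secondary threshold | 0.0125 | Statistical methods {20a} |
| Sample size | 50 before attrition; effect size 0.30, power 95%, alpha 0.05 | Sample size {14} |
| Correlation between the day 10 and day 38 tests | not stated; assumed 0 to 0.9 | assumption |

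**2. Do the plan's own figures show which design was meant?**

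*Secondary threshold.* 0.05 / 4 = 0.0125. Four measures are listed as secondary: SST, BPI-S, the adverse effects questionnaire and the acceptability questionnaire. The threshold therefore matches a count by instrument. It says nothing about MOAS visits.

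*Sample size.* For the group-by-time test of a repeated measures ANOVA, the noncentrality is lambda = f² × N × m / (1 − rho), where m is the number of measurements and rho their correlation. With f = 0.30, power 95% and alpha 0.05:

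- m = 2: N = 40 at rho = 0.5, and N = 50 at rho = 0.35.
- m = 3: N = 32 at rho = 0.5, N = 52 at rho = 0.15, and N = 48 at rho = 0.20.

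A total near 50 can be reached with two or three measurements. The article gives neither m nor rho, so the figure cannot be confirmed and does not settle the question.

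**3. Error rate if either visit may count**

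Let Z1 and Z2 be the test statistics at day 10 and day 38, with correlation r under no treatment effect.

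- Two-sided: P(|Z1| > 1.96 or |Z2| > 1.96). At r = 0 this is 1 − 0.95² = 0.0975.
- Favouring active tDCS only: P(Z1 > 1.96 or Z2 > 1.96), with Z signed so that positive favours active. At r = 0 this is 1 − 0.975² = 0.0494. The single-test value is 0.025.

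For r above 0, the bivariate normal distribution gives:

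| r | Two-sided (nominal 5%) | Favouring active (nominal 2.5%) | Two-sided, each visit at 0.025 |
|---|---|---|---|
| 0 | 9.75% | 4.94% | 4.94% |
| 0.3 | 9.51% | 4.76% | 4.84% |
| 0.5 | 9.07% | 4.54% | 4.65% |
| 0.7 | 8.35% | 4.17% | 4.30% |
| 0.8 | 7.81% | 3.90% | 4.02% |
| 0.9 | 7.04% | 3.52% | 3.62% |

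The value 0.5 is a natural reference. If the three MOAS scores have equal variances and a common correlation rho, the two changes from the shared baseline have correlation (1 − rho) / [2(1 − rho)] = 0.5 whatever rho is. With baseline as a covariate instead, the correlation is rho / (1 + rho): 0.23, 0.33 and 0.41 for rho = 0.3, 0.5 and 0.7. All of these lie inside the range shown.

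**4. Power cost of 0.025 per visit**

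Take N = 50, m = 2 and an assumed rho = 0.5, with 1 and 48 degrees of freedom.

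- If 0.30 is Cohen's f: lambda = 0.09 × 50 × 2 / 0.5 = 18. Power per test is 98.6% at 0.05 and 97.1% at 0.025.
- If 0.3 is Cohen's d, as Sample size {14} also calls it, f = 0.15 and lambda = 0.0225 × 50 × 2 / 0.5 = 4.5. Power per test is 54.7% at 0.05 and 43.0% at 0.025.

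**The case against.** The strongest reply is that the article never states two primary tests. A reader might infer from the sentence on separate treatment that day 10 and day 38 each get their own test at 0.05. The text does not support that as fact. The sentence covers MOAS, SST and BPI-S together, and SST has only one post-treatment measurement (day 3), so separation by visit cannot apply to it. Separation by instrument fits all three and agrees with 0.05 / 4. This objection stands: two separate 0.05 tests are not stated, and a single joint test over all times would hold 5%.

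It does not rescue the plan. Read by instrument, the 2 × 2 model still needs one post-treatment MOAS value and the article does not identify it. The choice between visits stays open.

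It is also fair to say that success is defined in one direction, so the chance of a false claim of benefit stays below 5% even in the worst case. That is correct, but the proper comparison there is 2.5%, and the relative inflation is much the same.

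Two further inferences should be resisted:

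- **That day 10 is a weak endpoint because incidents are rare.** Entry requires "a history of at least one incident of aggression in the last month", which is a minimum and not an expected rate. MOAS is a weighted severity score over four domains, including verbal aggression, and not a count of incidents. The article gives no recall window for it. No probability of an empty observation period can be derived.
- **That the two BPI-S visits break the secondary correction.** The secondary success criteria named are BPI and SSRT. Two BPI-S visits and one SSRT test make three tests, and 0.0125 already covers four. No shortfall is shown.

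**Conclusion.** The point holds in this form: the stated primary model conflicts with the stated schedule, and the deciding post-treatment value or contrast is undefined. That much rests on the text alone.

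The size is conditional. If success at either visit may be claimed, the two-sided primary type I error is about 7.0% to 9.75% instead of 5%, and 9.1% at a correlation of 0.5. In the direction favouring active tDCS it is about 3.5% to 4.9% against 2.5%. These figures assume normally distributed test statistics and a correlation between 0 and 0.9, which the article does not give. If one visit, an average or a joint test is fixed in advance, there is no inflation from this source. It would be wrong to report that the plan's error rate is nearly doubled as a settled fact; the plan permits that outcome but does not prescribe it.

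**What to change.** 1. **Reconcile the assessment details first.** Outcomes {12} has care staff complete MOAS at every visit. Participant timeline {13} has staff complete it at baseline and 1 week, then says participants complete it at 1 week and 1 month and are debriefed to unblind them. Who will be blinded {17a} says the professionals who rate MOAS are blinded and that participants are unblinded only after a serious adverse reaction. As written, the rater and the blinding at day 38 are unclear, so day 38 should not be adopted as primary by default.

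2. **Replace the 2 × 2 model for MOAS** with one model holding all three times: baseline MOAS and the planned BIS-11 total as covariates, day 10 and day 38 as repeated outcomes, and a group-by-visit term.

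3. **Name one primary contrast at 0.05 before the data are seen:** either active minus sham at one named visit, with the other visit secondary, or active minus sham averaged over the two visits. Alternatively, test each visit at 0.025, which keeps the two-sided error at or below 4.94% over the range examined.

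4. **Say what the separate treatment of post measures refers to,** by instrument or by visit.

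**Cost.** Items 2 to 4 change wording only; no visit or measurement is added. With a single named visit, the other no longer counts as primary. With 0.025 per visit there is a loss of power per test: 98.6% to 97.1% if 0.30 is Cohen's f, but 54.7% to 43.0% if it is Cohen's d (N = 50, assumed correlation 0.5). That difference favours a single contrast unless the effect size is confirmed as f.

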### Interim analyses {21b}

Interim analysis will be conducted once half (30) of the participants have been recruited. Study team members will perform this interim analysis. Stopping rules include: withdrawal of consent, development of a coincidental health problem/illness, exacerbation of aggressive behaviours expressed as a report of a serious violent incident and/or an increased incidence of self-harm or self-injurious behaviour. The principal investigator and the Research Ethics Board will make the final decision about early trial termination.

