### Criteria for discontinuing or modifying allocated interventions {11b}

Discontinuation rules for individual participants include withdrawal of consent, development of a coincidental health problem/illness, or exacerbation of aggressive behaviours expressed as a report of a serious violent incident and/or an increased incidence of self-harm or self-injurious behaviour as judged by their caregivers. Additionally, the study could stop early if the intervention significantly exacerbates aggressive, impulsive, or self-harming behaviours as judged by the trial investigators.

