### Sample size {14}

A power calculation conducted using repeated measures ANOVA (G*Power) yielded a total sample size of 50 participants (effect size=0.30, power=95%, *α* = 0.05). To allow for an attrition rate of 20%, we will aim to recruit 60 participants (30 per arm). These parameters were based on other studies involving the use of tDCS to modulate cognitive and behavioural functioning [30, 31]. Indeed, Minarik and colleagues [30] recommended small to intermediate effect sizes (between *d*=0.4 and *d*=0.5) for tDCS studies. We opted for an effect size of *d*=0.3 to improve precision. Furthermore, sample size calculation by Cosmo and colleagues [31] yielded 25 participants per arm for a power of 80% and bidirectional type I error probability of 0.05%. To allow for an attrition rate of 20%, a final sample size of 60 was considered sufficient by Cosmo and colleagues to detect a 50% difference in performance on the inhibitory control task in the active tDCS group, and a 10% difference in the sham tDCS group. While we acknowledge the importance of accounting for clustering by in-patient/care home, given our clinical experience, we anticipate that most of the participants will be recruited from the community. Furthermore, given the special nature of the population in this study and the funding constraints, it would be unrealistic to aim to recruit larger numbers. Nevertheless, we believe that the sample size of 30 participants per study arm is sufficiently large to detect differences between the effects of active and sham tDCS.

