### Composition of the data monitoring committee, its role, and reporting structure {21a}

The research management group will be responsible for data monitoring. While we acknowledged that data monitoring is best conducted by an independent committee, financial constraints precluded the appointment of such committee. However, as mentioned earlier, robust research governance procedures are in operation at Queen’s University and Providence Care Hospital to ensure the quality of study conduct.

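### The interim stopping rules repeat the discontinuation rules for individual participants and leave out the protocol's own trial-level harm criterion

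*Protocol article*

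**What the plan says.** Two sections of the protocol article bear on stopping.

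**Criteria for discontinuing or modifying allocated interventions {11b}** separates two levels.
- For the individual: "Discontinuation rules for individual participants include withdrawal of consent, development of a coincidental health problem/illness, or exacerbation of aggressive behaviours". Exacerbation is shown by a report of a serious violent incident and/or "increased incidence of self-harm or self-injurious behaviour as judged by their caregivers".
- For the trial: "the study could stop early if the intervention significantly exacerbates aggressive, impulsive, or self-harming behaviours as judged by the trial investigators".

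**Interim analyses {21b}** sets the only planned interim look: "Interim analysis will be conducted once half (30) of the participants have been recruited". Study team members perform it. The section then says: "Stopping rules include: withdrawal of consent, development of a coincidental health problem/illness, exacerbation of aggressive behaviours", with exacerbation again shown by a serious violent incident and/or more self-harm. The next sentence is: "The principal investigator and the Research Ethics Board will make the final decision about early trial termination".

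On oversight, the section on the data monitoring committee {21a} says: "The research management group will be responsible for data monitoring". It adds that funds did not allow an independent committee.

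**The concern.** A rule for stopping a trial should respond to evidence that the intervention does harm. A rule for stopping one person's treatment should respond to that person's state. The list in {21b} is of the second kind, but it stands where the first kind belongs, directly before the sentence on early trial termination.

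The one criterion that the protocol does set for the trial, significant worsening caused by the intervention, is in {11b} and is not repeated in {21b}. At stake is whether those who run and act on the interim look have a stated criterion that bears on the decision. This matters somewhat more here because study team members do the analysis, the research team is unblinded (Participant timeline {13}) and no independent committee reviews the result.

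**Working it through.** **1. The plan's own figure.** The target is 60 participants (Sample size {14}), and 60/2 = 30, which agrees with {21b}. With 1:1 allocation ({13}) that is about 15 per arm.

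**2. The two lists side by side.**

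| Item | {11b}, individual | {11b}, trial | {21b}, interim |
|---|---|---|---|
| Withdrawal of consent | yes | no | yes |
| Coincidental illness | yes | no | yes |
| Serious violent incident | yes | no | yes |
| More self-harm | yes, judged by caregivers | no | yes, no judge named |
| Intervention significantly worsens aggressive, impulsive or self-harming behaviours | no | yes, judged by investigators | no |

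The {21b} list has the same items in the same order as the individual list. It drops only the reference to caregivers. The single trial-level row is empty for {21b}.

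**3. What each item can show.** Withdrawal and coincidental illness carry no information on whether tDCS harms. A serious violent incident or more self-harm, read as in {11b}, is an event in one participant, in either arm. Entry requires at least one incident of aggression in the last month (Eligibility criteria {10}), so some incidents under sham are plausible.

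**4. How often the list is met when tDCS does nothing.** The document gives no rate of serious incidents or increased self-harm, so the per-participant risk p is assumed and shown as a range. For independent participants with equal risk in both arms, P(at least one of 30) = 1 − (1 − p)^30.

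| Assumed p | Calculation | P(at least one of 30) |
|---|---|---|
| 1% | 1 − 0.99^30 | 26% |
| 2% | 1 − 0.98^30 | 45% |
| 5% | 1 − 0.95^30 | 79% |
| 10% | 1 − 0.90^30 | 96% |
| 20% | 1 − 0.80^30 | 99.9% |

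The 20% row also applies to the withdrawal and illness items if all of the 20% attrition planned in {14} arises that way, which is an upper assumption.

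**5. Does meeting the list separate harm from no effect?** With 15 per arm, P = 1 − (1 − p_sham)^15 × (1 − p_active)^15. Take sham at an assumed 10%:
- active 5% (benefit): 1 − 0.9^15 × 0.95^15 = 1 − 0.206 × 0.463 = 90%
- active 10% (no effect): 1 − 0.206 × 0.206 = 96%
- active 20% (harm): 1 − 0.206 × 0.035 = 99%

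The list is met about as often under benefit as under harm.

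**6. What a comparison by arm can do at this size.** Take, purely for illustration, a rule that refers the trial if at least 4 more active than sham participants have an incident. Exact binomial sums with 15 per arm show that a doubling of risk triggers it in 3% (5% to 10%), 20% (11.9% to 23.8%) and 59% (27.1% to 54.2%). A fixed count therefore misses 97%, 80% and 41% of such harm. A comparison by arm addresses the right question, but a hard count threshold at 30 participants is a weak safeguard.

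**The case against.** Several points on the other side stand.

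- **The trial-level criterion exists.** It is in {11b}, and the verb *include* in {21b} leaves the list open. A reader might infer that the plan has no criterion for stopping the trial. It has one; it is missing only from the section that governs the interim decision.
- **Nothing forces a stop.** A reader might take the figures above as the chance of stopping the trial wrongly. They are only chances that at least one participant meets an item. The principal investigator and the Research Ethics Board decide, and they would be unlikely to stop for one withdrawal.
- **The incident rates are assumed.** At 1% the chance of at least one event is 26%, so the incident items alone do not make it near certain that the list is met.
- **Safety oversight is wider than the interim look.** The management group meets monthly ({5d}), hospital coordinators monitor safety when serious adverse effects are reported or at least every 6 months ({23}), and adverse events go to the Research Ethics Board ({22}).
- **Thresholds can live elsewhere.** An article may leave numerical boundaries to the full protocol, so their absence is no fault.

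None of this removes the core point. The article does state stopping rules for the interim analysis, and the stated items belong to another level. An open list does not make consent withdrawal a reason to end a trial. A later document could add a threshold, but it would still have to set aside the items listed here. If the deciders ignore those items, as they should, the interim section leaves them no usable criterion.

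**Conclusion.** The concern holds as a fault of level. Section {21b} presents participant-level discontinuation rules as the stopping rules of the interim analysis and does not carry over the trial-level criterion of {11b}. That conclusion rests on the text alone and needs no assumed rate.

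The size of the problem does rest on assumptions: independent participants, about 15 per arm at the interim, and incident risks that the document does not give. Under no effect, the chance that at least one of 30 has a trigger incident runs from 26% at 1% risk to 79% at 5% and 99.9% at 20%. With sham at 10%, the chance moves only from 90% under benefit to 99% under harm.

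The consequence is limited. The documents do not show that a wrong stop is likely, and the primary analysis is unaffected. Severity: minor.

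**What to change.** In {21b}, delete withdrawal of consent, coincidental illness and the single-participant incident items; they stay in {11b}. Put the trial-level criterion in their place, for example: *The principal investigator and the Research Ethics Board will consider early termination if aggressive, impulsive or self-harming behaviours are significantly worse in the active than in the sham arm, based on incident counts and outcome scores compared by arm at the interim.*

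No fixed count threshold is needed.

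The cost is one or two sentences and no new data, since the incidents and scores are already collected. The limitation is that about 15 participants per arm will miss moderate harm, so the Board's judgement remains necessary.
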